
The KHQ has been translated and validated into the Portuguese language [31]. This questionnaire is specific to UI [32]. The KHQ consists of 30 questions, divided into eight domains: general health perception, impact of UI, limitations of daily activities, physical limitations, social limitations, personal relationships, emotions, sleep/mood. The questionnaire also contains two other independent scales: one assesses the severity of UI (severity measures) and the other the presence and intensity of urinary symptoms (urinary symptom scale). The KHQ is scored in domains, so there is no overall score. The scores range from 0 to 100 and the higher the score obtained, the worse the quality of life related to that domain [31].

The 24 h-VD [3], contains data on urinary habits, and should be completed for a period of 24 hours, with information on number of urinations; amount of urine eliminated; and occurrence of urinary loss or urgency. During the study, the participant will complete the diary 3 times, referring to pretreatment, middle of treatment (6th session), and end of treatment (12th session).

During the treatment, in order to follow the micturition symptoms per session, a Session Monitoring Card will be used. This fact sheet contains open and closed questions about the urinary symptoms of the day before the session and the day of the session. It also contains a Visual Analogue Scale (VAS) [33] to indicate possible discomfort of the applied technique. The volunteer will be questioned as to their degree of discomfort during the treatment, with 0 indicating total absence and 10 the maximum level of discomfort bearable. Any side effects that the participants report will be recorded by the researcher. Over the 12 sessions, each participant will complete 12 Session Monitoring Cards, thus allowing longitudinal analysis of the voiding symptoms.

One month after completion of treatment, an investigator, blinded to the allocation of participants, will complete a Follow-up Monitoring Card. In addition to this card, the ICIQ-OAB and OAB-V8 will also be applied.

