### Measurement of results, primary and secondary outcomes

The outcome measures will be evaluated in several stages: at the beginning before the randomization (Anamnesis record, OAB-V8, ICIQ-OAB, KHQ, 24 h-VD), during the 12 sessions (Session Monitoring Card), in the 6th and 12th sessions (OAB-V8, ICIQ-OAB, KHQ, 24 h-VD), and 30 days after the end of treatment (Follow-up Monitoring Card, OAB-V8, ICIQ-OAB) (Table 1). The primary outcome of the study is urgency, measured by the OAB-V8. This was chosen as it is a validated instrument for Portuguese, with criteria defined for identification of urgency, easy to apply, objective, with robust results. It is used both as a screening tool and to raise self-identification awareness of the participant. In addition, as a primary outcome, the number of episodes of urgency will be observed (obtained in the Session Monitoring and Follow-up sheets). As secondary outcomes: voiding habits (number of diurnal urinations (Session Monitoring and Follow-up sheets and ICQ-OAB), use of absorbent pads (KHQ), urinary incontinence (number of episodes of urinary loss Session Monitoring and Follow-up sheets and ICIQ-OAB, severity of UI (ICIQ-OAB)) and quality of life (KHQ and ICIQ-OAB).

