### Statistical analysis plan

The statistical analysis will be performed by a statistician blind to the allocation of the groups and without involvement in the research. The software SPSS 16.0 and R 3.5.1 will be used for the analysis of data (IBM SPSS Statistics, Armonk, NY, USA). The level of significance will be set at 5%. The normality of the residues will be verified by the Shapiro-Wilk test.

The comparison of urgency, voiding habits, UI, and quality of life between groups (TTNS, PTES, and placebo) and between stages (pretreatment, 6th and 12th evaluation, follow-up), as well as the interactions between these will be performed by means of ANOVA of mixed models considering group and time factors for repeated measures if the residuals present normality with post hoc contrasts (treated versus placebo group, TTNS versus PTES).

The first statistical procedure will be to verify, in general and at each evaluation stage (pretreatment, 6th and 12th evaluation, follow-up) if the urgency, voiding habits, UI, and quality of life differ in the TTNS and PTES groups compared to the placebo group. The null hypothesis is that in both the TTNS group and the PTES group, urgency, urinary habits, urinary incontinence, and quality of life will be the same as the placebo group. The alternative hypothesis is that the TTNS and PTES groups will differ from the placebo group.

The second statistical procedure has the intention of verifying whether, in general and at each stage of evaluation (pretreatment, 6th and 12th evaluation, follow-up), urgency, voiding habits, UI, and quality of life differ between the TTNS group and the PTES group. The null hypothesis is that in both the TTNS group and the PTES group the behavior is the same. The alternative hypothesis is that there is a difference in behavior between these two groups.

The third statistical procedure aims to verify if there is alteration in the urgency, voiding habits, UI, and quality of life throughout the four stages of study evaluation (pretreatment, 6th and 12th evaluation, follow-up) within each of the groups. The null hypothesis is that the behavior is the same throughout the stages in each group. The alternative hypothesis is that there is a difference in the stages in each group.

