The fourth statistical procedure is to verify if there is a change in the urgency, voiding habits, and IU throughout the 13 study evaluation stages (being the 12 session monitoring cards and 1 follow-up monitoring card) within each of the groups. The null hypothesis is that the behavior is the same throughout all stages in each group. The alternative hypothesis is that there is a difference throughout the stages in each group.

The quantitative variables will be presented as minimum value, maximum value, mean, median, standard deviation, coefficient of variation, and asymmetry coefficient. Categorical variables will be presented as frequencies and percentages.

Details of the statistical analyses are shown below:

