In the interview, the anamnesis record will be applied, which generates qualitative variables that will be presented as frequencies and percentages, and quantitative variables that will be presented as minimum value, maximum value, mean, median, standard deviation, coefficient of variation, and asymmetry coefficient. The ICIQ-OAB, KHQ, OAB-V8, and 24 h-VD will be applied, which will result in quantitative scales that will be presented as minimum value, maximum value, mean, median, standard deviation, coefficient of variation, and asymmetry coefficient.In the 6th and 12th sessions, the ICIQ-OAB, KHQ, OAB-V8, and 24 h-VD will be applied, which will result in quantitative scales that will be presented as minimum value, maximum value, mean, median, standard deviation, coefficient of variation, and coefficient of asymmetry.In the follow-up, the ICIQ-OAB, OAB-V8 and Follow-up Monitoring Card will be applied, which will result in quantitative scales that will be presented as minimum value, maximum value, mean, median, standard deviation, coefficient of variation, and coefficient of asymmetry.In all sessions during the treatment, a Session Monitoring Card will be applied that will generate quantitative variables that will be presented as minimum value, maximum value, mean, median, standard deviation, coefficient of variation, and coefficient of asymmetry.At the end of the treatment, the ANOVA for repeated measurements will be applied to verify the effects of the three groups and the three stages (pretreatment, 6th and 12th evaluation), and the interactions between them in the KHQ, ICIQ-OAB, OAB- V8, and 24 h-VD, if the residues present normality. If the residues do not present normality, a non-parametric test will be applied.At the end of the sessions and follow-up, the ANOVA for repeated measures will be applied to verify the effects of the three groups and the four stages, and the interactions between them in the OAB-V8, ICIQ-OAB, and Monitoring Cards (sessions and follow-up), if the residues present normality. If the residues do not present normality, a non-parametric test will be applied.At the end of the sessions and the follow-up, the ANOVA for repeated measurements will be applied to verify the effects of the 13 stages (12 sessions and follow-up) of the Monitoring Cards (sessions and follow-up), if the residues present normality. If the residues do not present normality, a non-parametric test will be applied.

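### The only analysis that uses all 13 Monitoring Cards compares stages, not arms, so most session cards for a primary outcome never inform the randomised comparison

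*Protocol article*

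**What the plan says.** All references are to the Protocol article.

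- Measurement of results, primary and secondary outcomes: besides the OAB-V8, "In addition, as a primary outcome, the number of episodes of urgency will be observed (obtained in the Session Monitoring and Follow-up sheets".
- Evaluation tools: "Over the 12 sessions, each participant will complete 12 Session Monitoring Cards". Each card asks about "urinary symptoms of the day before the session and the day of the session". One further card is completed a month after treatment.
- Statistical analysis plan, main model: groups are compared, and time points are compared "between stages (pretreatment, 6th and 12th evaluation, follow-up", with contrasts of treated against placebo and TTNS against PTES.
- Statistical analysis plan, details: the repeated-measures ANOVA that includes the cards tests "the effects of the three groups and the four stages, and the interactions between them in the OAB-V8, ICIQ-OAB, and Monitoring Cards".
- Statistical analysis plan, fourth procedure: it looks for change over the "13 study evaluation stages (being the 12 session monitoring cards and 1 follow-up monitoring card) within each of the groups". The matching item in the details is "ANOVA for repeated measurements will be applied to verify the effects of the 13 stages (12 sessions and follow-up) of the Monitoring Cards". It mentions neither the three groups nor an interaction.

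**The concern.** The placebo arm is there so that the effect of stimulation can be separated from placebo response, natural fluctuation and regression to the mean. Women enter with an OAB-V8 score of at least 8, so some fall in symptoms can be expected in every arm. A test of whether the episode count changes over 13 stages within an arm picks up all of these together. It cannot attribute any of the change to TTNS or PTES.

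Yet that uncontrolled test is the only inferential use the plan makes of most session cards for one of its two primary outcomes. Each card covers about two days, so a single card is a short sample of a woman's symptoms. The TTNS-PTES comparison, on which the trial's hypothesis of similar benefit rests, draws on the same few cards.

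**Working it through.** **1. Which cards enter a comparison between arms.** The four stages are pretreatment, 6th session, 12th session and follow-up. Session cards used: 2 of 12, so 12 − 2 = 10 are unused. Table 1 schedules no Monitoring Card at pretreatment, so the first of the four stages is undefined for this outcome. If the session-1 card takes that place, 12 − 3 = 9 are unused.

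**2. Is the group factor really absent?** Three consecutive items in the details can be set side by side. The item for the end of treatment names three groups, three stages and their interactions. The next names three groups, four stages and their interactions. The third names the 13 stages only.

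**3. The plan's own figure.** Sample size section: 3 groups, 4 stages, f = 0.15, 5% level, 90% power, N = 99. Assume correlation 0.5 and sphericity (neither is stated) and take the group-by-stage test:
- λ = f²·N·4/(1 − ρ) = 0.0225 × 99 × 4/0.5 = 17.82, on 6 and 288 degrees of freedom.
- Power is 0.900 at N = 99 and 0.889 at N = 96. The stated size reproduces, and this point does not touch it.

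**4. Precision with a constant effect (assumed).** One active arm against placebo, 33 v 33, two-sided 5%, difference 0.5 SD. Under compound symmetry, the variance of a mean of m cards, relative to one card, is (1 + (m − 1)ρ)/m. The noncentrality is 0.5·√(33/2)/√variance, on 64 degrees of freedom. The starting point is the mean of the three post-start cards that the plan uses (6th, 12th, follow-up).

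| ρ | 3 planned cards | Cards 6-12 (7) | All 13 cards |
|---|---|---|---|
| 0.5: variance | 0.667 | 0.571 | 0.538 |
| 0.5: power | 68.8% | 75.4% | 77.8% |
| 0.8: variance | 0.867 | 0.829 | 0.815 |
| 0.8: power | 57.5% | 59.4% | 60.1% |

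**5. Precision with a gradual effect (assumed).** Solving f² = δ²·(2/9)·var(t) with t = (0, 0.5, 1, 1), where var(t) = 0.1719, gives δ = 0.768 SD at session 12.
- 12th-session contrast, already planned: 86.7% at any ρ.
- Mean of the three planned cards: 88.0% (ρ = 0.5), 81.6% (0.7), 78.5% (0.8).
- Mean of cards 6-12: average effect 0.75δ; power 86.1%, 76.2%, 71.6%.

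So an average over sessions is no better than the planned contrasts here. For an equal-weight mean of all 13 cards, with the effect rising from zero at session 1 and ρ = 0.5, power falls from 80% to about 54%.

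**6. The group-by-stage test itself.** Let both active arms rise linearly from 0 at session 1 to 0.6 SD at session 12, held at follow-up. Then λ = 33 × 0.6² × (2/3) × Σ(t − t̄)²/(1 − ρ).
- Four stages (session 1, 6, 12, follow-up): Σ = 0.700; at ρ = 0.5, λ = 11.1 on 6 and 288 df; power 69%.
- Thirteen stages: Σ = 1.413; λ = 22.4 on 24 and 1152 df; power 79%.
- At ρ = 0.7 the same comparison gives 91% and 97%.

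**The case against.** **Fixed comparison times are a legitimate choice.** The Discussion says change in urgency will be looked for at the 6th and 12th sessions and a month after treatment, and names the cards among the tools. This stands. It is a reason to keep those contrasts, not a reason to analyse the full series without a comparator.

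**The group factor may only be unmentioned.** The third procedure also speaks of change within each group, although its model has group and interaction terms, and a fuller plan may exist. This stands in part: the phrase alone would not settle the matter. The weight lies on the details, where the 13-stage item drops the groups and interactions that the two items before it name. If a group term is intended, the fix is only a clarification.

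**The power gain may be overstated.** A reader might compare the mean of cards 6 and 12 with the mean of cards 6-12, see power rise from 75.8% to 86.1% under a gradual effect at correlation 0.5, and conclude that the planned contrasts should be replaced. The documents do not support this. The plan never averages cards 6 and 12. It compares arms at each stage and includes follow-up. Against those contrasts (86.7% and 88.0%) the cards 6-12 mean gains nothing. With correlation that decays between sessions and a constant effect, a plain 13-card average can also lose slightly: 80% to 78% when the correlation is 0.7 over three sessions. This objection stands in full.

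**Conclusion.** The point holds as a design weakness in the analysis. As written, 10 of the 12 session cards (9 if session 1 is the baseline) for a primary outcome inform only change within arms, which cannot separate TTNS or PTES from placebo.

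The direction of any gain in precision depends on the method, and its size on quantities that the article does not state for the episode count: SD, correlation between cards, and time course. Under compound symmetry and a constant 0.5 SD effect, the gain over the three planned cards is about 7 to 9 points at correlation 0.5 and about 2 to 3 points at 0.8. For the group-by-stage test with a 0.6 SD gradual effect it is about 6 to 10 points.

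A reader might infer that power is certainly lost, or that N = 99 is wrong. Neither follows: the gain can vanish or reverse for a plain average, and N = 99 reproduces for the four-stage design. The case for the change is that it turns an uncontrolled test into a randomised comparison; extra power is a possible further benefit.

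**What to change.** In the Statistical analysis plan section, change the fourth procedure and its matching item in the details as follows:

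- Make the 13-stage Monitoring Card analysis a mixed model with three groups and 13 stages: group, stage and group-by-stage.
- Report TTNS v placebo, PTES v placebo and TTNS v PTES from it.
- Keep the planned 6th-session, 12th-session and follow-up contrasts. Do not replace them with a mean over cards 6-12 or over all cards.
- State which card, if any, is the pretreatment stage for the episode count, since Table 1 schedules none.

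Cost: revised wording, slightly more analysis work and one more model to report. No new data, visits or participants are needed. The Trial status section says that no analysis has yet been performed, so the change can still be specified in advance.

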In the protocol of the present study, due to the nature of the applied therapy, it is not possible to blind the physiotherapist as well as the participants. Ussing et al. [43], in their protocol, discuss the difficulty of blinding participants and health professionals when examining a physiotherapeutic intervention. In the study of these authors, in a similar way to the present study, the participants were blinded in relation to the hypothesis of the study. Participants are not informed, either verbally or in writing, that we expect electrostimulation to be more or less efficient between groups.

It should be emphasized that, based on the possibility of confirming the hypothesis that urgency will decrease in a similar way after both treatments (TTNS and PTES), the PTES will be used as an option for positioning the electrodes alternately to the tibial nerve region. Since people may have problems in the tibial nerve region such as sensitivity and skin changes, bilateral amputations, and in cases in which the patient does not present a good response with TTNS, PTES may be applied, with equally good responses to the traditional TTNS technique.

This knowledge will help to clarify the role of electrostimulation in the treatment of urgency symptoms and allow evidence-based recommendations on TTNS and PTES as part of the first-line treatment for urgency and diseases such as UUI and OAB syndrome.

### Trial status

The protocol registration was approved on May 17, 2018, and is on version 2 (after the initial evaluation sessions, we computed the sample size calculation and we had to add three more participants, one per group). To date, we have enrolled 52 study participants who have completed treatment, assessments, and follow-up. The initial date of recruitment was June 1, 2018, and the approximate date of recruitment to be completed will be December 2019. Although existing data are being entered, no analysis has yet been performed.

## Data Availability

Not applicable.

## Abbreviations

24 h-VD: 24-Hour Voiding Diary
ANOVA: Analysis of variance
Hz: Hertz
ICIQ-OAB: Incontinence Questionnaire Overactive Bladder
ICT: Informed Consent Term
KHQ: King’s Health Questionnaire
LAMU: Laboratory of Research in Women’s Health
OAB: Overactive bladder
OAB-V8: Overactive Bladder – Validated 8-Question Awareness Tool
PSIS: Posterior superior iliac spine
PTES: Parasacral transcutaneous electrical stimulation
QoL: Quality of life
S2: Second sacral vertebrae
S3: Third sacral vertebrae
TTNS: Transcutaneous tibial nerve stimulation
UFSCar: Federal University of São Carlos
UI: Urinary incontinence
US: Ultrasound
UUI: Urgency urinary incontinence
VAS: Visual analogue scale
μs: Microseconds
